## Abstract

Psychosocial factors play an important role in non-communicable diseases (NCDs). This observational study is primarily aimed at assessing the relationship of psychological characteristics of patients with the outcomes of different NCDs, and to assess short-term psychotherapy (STP) efficacy in the real world. **Methods**: One hundred and forty patients with recent acute myocardial infarction, Takotsubo syndrome, or non-metastatic breast cancer and a control group of 140 age and sex-matched healthy subjects, will be enrolled. All subjects will be administered psychometric tests, quality of life tests, a specific body perception questionnaire, a dream questionnaire, and a projective test, the Six Drawing test at baseline and follow-up. All subjects with medical conditions will be asked to freely choose between an ontopsychological STP along with standard medical therapy and, whenever indicated, rehabilitation therapy or medical therapy plus rehabilitation alone. The study endpoints will be to evaluate: the relationship of the psychological characteristics of enrolled subjects with the outcomes of different NCDs, predictors of the choice of psychotherapy, and the efficacy of ontopsychological intervention on psychological and medical outcomes. **Conclusion**: This study will generate data on distinctive psychological characteristics of patients suffering from different CDs and their relationship with medical outcomes, as well as explore the efficacy of ontopsychological STP in these patients in the real world. (Number of registration: NCT03437642).

## 1. Introduction

Non-Communicable Diseases (NCDs) represent 71% of all global deaths, the two most prevalent being cardiovascular diseases (CVD) and cancer [1]. As such, psychosocial factors have gained a rising interest as therapeutic targets in NCDs.

Indeed, several psychological conditions can predispose, precipitate, and increase the risk of some of the most ominous cardiovascular diseases, such as ischemic heart disease (IHD) [2,3].

In oncologic disease, although there are no conclusive data providing a causal link with psychological variables, psychological factors play a pivotal role in diagnosis and therapy [4]. Therefore, systematic screening for distress and supportive care needs may be recommended for these patients.

Several studies have assessed psychotherapy intervention in cardiac patients in order to reduce stress and depression and improve medical prognosis [5,6,7,8], including morbidity and mortality, reported in a recent meta-analysis of randomized controlled trials for cardiac rehabilitation (CR) programs [9]. Recently, we demonstrated in the STEP-IN-AMI (Short TErm Psychotherapy IN Acute Myocardial Infarction) trial that adding short-term ontopsychological psychotherapy (STP) to standard medical therapy in post-acute myocardial infarction (AMI) patients improved psychological symptoms and quality of life at one year [10], as well as a composite endpoint of medical and cardiac outcomes at five years [11] independently of CR. However, studies are also needed to assess the generalizability of ontopsychological psychotherapy in IHD and control for possible bias due to randomization in psychological interventions.

Moreover, sub-analysis of STEP-IN-AMI trial data provided original insights on the relationship between emotions, dreams, and medical conditions suggesting new potential diagnostic, preventive, and therapeutic strategies. As this possibility may potentially extend to other NCDs, two clinical diagnoses appear to be ideal initial candidates to test this hypothesis in addition to ischemic patients: Takotsubo syndrome and breast cancer.

Takotsubo syndrome (TTS) often mimics acute myocardial infarction, but it is not caused by an obstruction of epicardial coronary arteries and generally spontaneously heals in survivors [12,13,14,15,16]. In many cases, there is a clear and identifiable psychological or physical “trigger” for TTS. Surprisingly, no psychotherapeutic approach has been attempted in this patient population.

Breast cancer (BC) is also an ideal case study because it has been extensively investigated from a psychosocial point of view and represents a public health priority in women worldwide. Several psychological factors such as depression, hopelessness [17], anxiety, intrusive thoughts, social support [18,19], fear of recurrence [20], compassion [21], and sentimental issues [22] are known to play a complex role in the follow-up of patients with breast cancer, interfering with the quality of life, therapeutic choices, and worsening prognosis. Patients’ experience of therapeutic side effects can deeply affect body image and self-esteem [23,24,25], and while reconstructive surgery is of great importance [26], it is not known whether such surgery is sufficient to generate an experience of comprehensive healing which may impact treatment outcome.

Based on previous data from the STEP-IN-AMI trial, we have designed an observational study to obtain additional psychosomatic insights and assess the effects of ontopsychological STP in acute MI, Takotsubo, and breast cancer patients.

## 2. Materials and Methods

PSYCHONIC (PSYChosomatic medicine in ONcologIc and Cardiac disease), is a retrospective and prospective observational case-control study, approved by the relevant ethical committee (Comitato Etico Lazio 1) on 12 May 2017, amended on 9 October 2017, and registered in www.clinicaltrial.gov on 27 March 2018 (number of registration: NCT03437642). The study is compliant with the Code of Helsinki.

### 2.1. Aims

(1)To prospectively assess the clinical and psychological characteristics at enrollment, and the real-world outcomes at one and five years in patients (pts) with AMI, TTS, and BC who (a) have undergone ontopsychological STP or (b) declined the treatment, as well as (c) a control group of age/sex-matched subjects without major active diseases (for a practical exposition they are referred to as “Healthy Subjects”, HS) not undergoing psychotherapy at enrollment(2)To assess:
The perception of their body and emotions in each group at baseline and follow-up;Dream symbols and patterns in each group, including retrospective evaluation of past dreams (until childhood and adolescence), at baseline and follow-up;Specific psychodynamic patterns in each group based on personal history, dream analysis, psychometric tests, and the projective non-structured Six Drawing test (6DT) [27,28];The correlation of past dream symbols and patterns with the onset of disease in each group;The correlation between baseline psychological data/evaluations and study outcomes.

#### The Rationale for the Study Aims

As specified above, the PSYCHONIC study has been inspired by the results of the previously published STEP-IN-AMI trial (Short TErm Psychotherapy IN Acute Myocardial Infarction).

The STEP-IN-AMI trial randomized 101 pts with AMI to standard medical therapy or standard care plus original short-term psychotherapy derived from the ontopsychological method (STP) [10]. Ontopsychological psychotherapy is a humanistic existential-psychotherapy associated with psychodynamic analysis [29] (for a detailed description see the paragraph dedicated to “therapies”). Compared to controls, patients who underwent STP showed a statistically significant improvement in psychological symptoms (reduction in depression scores, assessed by the Beck Depression Inventory {BDI}) [30,31], improvement in quality of life at a one-year follow-up as assessed by the MacNew Heart Disease Health-Related Quality of Life Questionnaire [32], and a statistically significant improvement in medical and cardiac prognosis (reduction of angina incidence, new comorbidities, and new admissions for cardiac and other medical events) at five years’ time [11]. Despite the high internal validity of this study, ontopsychological STP outcomes remain to be assessed in the real world where the active choice of therapy by the patient has a pivotal role in intervention efficacy.

Moreover, the encouraging results of the STEP-IN-AMI trial suggest that several specific psychosomatic issues deserve further evaluation in a wider clinical context to assess new potential diagnostic, preventive, and therapeutic strategies which may potentially extend to other diseases. Particularly, the study analysis revealed for the first time two main psychological patterns:(1)Poor awareness of emotions, which may have reflected a lack of the perception of one’s body, or parts of one’s body. Patients seemed to have a painful perception of parts of their body (mainly the head and/or the chest, with particular reference to their heart), whereas they did not have a perception of other parts, as if they were “anesthetized”. In the STEP-IN-AMI pts, there was an improvement of body/emotional perception during psychotherapeutic intervention with body relaxation training [33], conducted both in individual and group meetings. Patients were encouraged to explore their bodily sensations, starting with the visceral zone (i.e., abdomen), with the help of abdominal breathing. From our experience, abdominal breathing seems to act as a strong stimulus to the visceral brain, which is continuously active throughout one’s entire life (even if we have lost our conscious perception of it), and the subjective contact with the visceral zone translates as an important mediator of inner emotions and feelings [34].(2)An apparent presence of specific dream configurations in the period before AMI (i.e., distressing dreams or repeated nightmares; no memory of dream content; or selective memory only of dreams of childhood and adolescence), which again improved when recovering from the acute event in those undergoing STP [10,11].

Following observations from ontopsychology, the dream pattern seems to follow a hierarchical approach [27]. In particular, the unconscious dynamics of the dream seem to primarily aim at the optimal psycho-physical evolution of the dreamer, the basic one being the biological aspect represented by the dreamer’s health. Following this point of view, at least in our observations, specific dream patterns may be ahead by months or years of the acute cardiac event as if the dream symbols reflect how the dreamer is behaving towards his/her health (concerning both lifestyle and choices/decisions in his/her existential context).

No studies have addressed the issue related to dream patterns in cardiac patients, and in psychosomatics in general.

Similarly, no studies have addressed a systematic and comprehensive psychodynamic profile of patients suffering from different diseases to guide prevention and therapies.

### 2.2. Participants

#### 2.2.1. Inclusion Criteria

(1)Patients with AMI with ST-elevation on the admission electrocardiogram (STEMI) and without ST elevation (NSTEMI) treated with urgent percutaneous coronary intervention (PCI); up to 12 h for STEMI and 48 h for NSTEMI patients.

According to the Fourth Universal Definition of Myocardial Infarction, acute myocardial injury is defined as the presence of either positive troponins with a rise-and-fall pattern, a fall-only pattern (in case the first available troponin was the peak), or a rise-only pattern [35,36].

(2)Patients with TTS

Diagnosis of TTS is based on the modified Mayo Clinic Diagnostic Criteria including (1) transient wall motion abnormality of the left ventricle with extension beyond a single epicardial coronary artery distribution; (2) absence of obstructive coronary artery disease or angiographic evidence of acute plaque rupture; (3) new electrocardiographic abnormalities or troponin value increase; and 4) the absence of myocarditis or pheochromocytoma at index hospitalization [12,37,38].

Although TTS was initially described with angiographically normal coronary arteries, smaller studies recently indicated a potential coexistence of coronary artery disease (CAD) in TTS patients [39]. To avoid confusion in the initial diagnosis, in this protocol TTS pts without critical coronary artery stenosis will be enrolled.

(3)Patients recently operated on for non-metastatic BC treated with radiotherapy and/or chemotherapy and/or hormone therapy.(4)A control group of subjects without major active diseases (HS), matched for age and sex. This includes subjects without clinical evidence of major diseases that required hospitalization in the last ten years or chronic medical therapy (e.g., anti-neoplastic, immunosuppressant, cortisone, psychiatric, etc.), and not undergoing or scheduled for psychotherapy at enrollment.

Inclusion criteria for all patient groups include an age between 30 and 75 years old, the ability to provide written informed consent to participate in the study, and availability to undergo psychotherapeutic treatment.

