#### 2.2.2. Exclusion Criteria

Patients with a disability, cognitive impairment, life-threatening conditions, or enrollment in another clinical study will be excluded.

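### The healthy-subject criterion looks back ten years for hospitalization and sets no lifetime exclusion of the index diseases, so a remote former case can serve as a control for lifelong dream and personal history

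*Protocol article*

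**What the plan says.** The control definition is in 2.2.1 (Inclusion Criteria). It opens with "A control group of subjects without major active diseases (HS), matched for age and sex" and is then spelled out as "subjects without clinical evidence of major diseases that required hospitalization in the last ten years or chronic medical therapy". The examples of therapy and a further condition follow: "e.g., anti-neoplastic, immunosuppressant, cortisone, psychiatric, etc.), and not undergoing or scheduled for psychotherapy at enrollment".

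The exclusion criteria (2.2.2) read "Patients with a disability, cognitive impairment, life-threatening conditions, or enrollment in another clinical study will be excluded". They do not mention a previous index disease.

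On design, section 2 says that PSYCHONIC "is a retrospective and prospective observational case-control study". Among the aims in 2.1 is the assessment of "Dream symbols and patterns in each group, including retrospective evaluation of past dreams (until childhood and adolescence), at baseline and follow-up". A further aim in the same list relates past dream symbols to disease onset. Section 3.1 confirms that the enrollment dream questionnaire goes to all four groups, healthy subjects included, and reaches back to childhood and adolescence.

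The Introduction says that Takotsubo syndrome "generally spontaneously heals in survivors".

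**The concern.** In a case-control comparison the controls should be free of the disease in question over the period in which the exposure is measured. Here the exposure runs from childhood onward, while the hospitalization limb of the control rule covers only the last ten years. A person whose index disease falls outside that window has already had the onset that the control is meant not to have had.

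The rationale under 2.1 suggests that dream patterns may precede an acute cardiac event by months or years. If something of that kind holds for the disease in question and is still recalled later, a former case would report the pattern under test while counted as healthy. That would pull the contrast towards no difference.

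The article also describes its controls more strictly elsewhere than the rule does: the Abstract calls them healthy, and the Discussion describes them as free of major diseases with no time limit. A reader of the results would probably assume that no control had ever had the index disease.

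**Working it through.** **1. Group size.** Sample Sizing gives 55 AMI, 55 breast cancer and 30 Takotsubo patients: 55 + 55 + 30 = 140, which reproduces the planned 140 healthy subjects (one per patient). Enrollment Status reports 41 healthy subjects enrolled, so 140 − 41 = 99 were still to come.

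**2. Who passes the rule as written.** The ten-year limit is attached to hospitalization. The chronic-therapy limb has no time limit and can be read as current therapy or as therapy ever required.

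| Former case, disease more than ten years ago | Therapy clause = current | Therapy clause = ever |
|---|---|---|
| Takotsubo, healed, never on chronic therapy | admitted | admitted |
| Breast cancer, prolonged anti-neoplastic or hormone therapy, now finished | admitted | barred |
| Breast cancer, treated without therapy that counts as chronic | admitted | admitted |

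The first row holds on either reading. The second depends on the reading. The article states an age range of 30 to 75 for patients and matches controls on age, so an episode more than ten years old is possible.

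**3. Which comparisons are touched.** The affected items are those on past years' dreams and personal history, for the disease that the former case once had. Items on the last week, month or year, the psychometric scores and the Six Drawing test describe the present state and are less affected.

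**4. Size, as illustration only.** The article gives no share of former cases. Let f be that share among the controls compared, p1 the frequency of a trait in cases and p0 its frequency in true controls. If former cases fully resemble cases, the observed contrast is

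p1 − [(1 − f)·p0 + f·p1] = (1 − f)·(p1 − p0).

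Assume p1 = 50% and p0 = 25% (not from the article), with 55 cases against 140 controls. Power = Φ[(difference − 1.96·SE0)/SE1], where SE0 uses the pooled and SE1 the separate variances. At f = 0, SE0 = 0.0743 and SE1 = 0.0767, so (0.25 − 1.96 × 0.0743)/0.0767 = 1.36, a power of 91%.

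| Assumed f | Former cases among 140 | Difference (points) | Power |
|---|---|---|---|
| 0 | 0 | 25.0 | 91% |
| 1% | 1.4 | 24.75 | 91% |
| 2% | 2.8 | 24.5 | 90% |
| 5% | 7 | 23.75 | 88% |
| 10% | 14 | 22.5 | 84% |

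Full resemblance is the worst case. With partial resemblance the loss is smaller.

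**The case against.** The strongest reply is that the therapy clause already does most of the work. In the sentence, the verb *required* can govern both hospitalization and chronic therapy, the ten-year limit attaches only to the former, and anti-neoplastic treatment is the first example given. On that reading many former breast cancer patients are barred for life. This stands as far as it goes: a reader might infer that any woman treated for breast cancer more than ten years ago is a valid control, and the text does not establish that. It is one of two readings, and the clause needs clarifying. The remote Takotsubo case passes either way.

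A second reply is that the rule is a disclosed choice. Controls are defined by the absence of active disease, the label of healthy subjects is used for convenience, and the work is called a pilot. A finite look-back also makes it easier to find matched controls at older ages. That is reasonable for measures of current state. The article gives no reason why ten years suits an exposure measured from childhood.

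A third reply is rarity. The Takotsubo group was held at 30 because few such patients are admitted, so a volunteer with a remote, untreated episode should be rarer still. This stands as well: nothing shows that even one former case is among the 41 controls enrolled, or would be among the 140.

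Finally, a reader might infer that every patient-versus-healthy contrast is biased. The article does not support that. The precursor pattern is proposed for the acute cardiac event, not for breast cancer, and it is reported to have improved during recovery in patients who had psychotherapy. That former cases still resemble cases a decade later is an assumption. A former case of one disease is also a misclassified control only for that disease, unless the patterns are shared across diseases.

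**Conclusion.** The point holds in a limited form. As written, the rule admits a person with a Takotsubo episode more than ten years ago and no chronic therapy. It also admits a former breast cancer patient off treatment if the therapy clause means current. That does not match a case-control comparison of lifetime recall. If former cases resemble cases, the effect is a slight dilution, towards no difference, of the lifetime-recall contrasts for the same disease. The size is unknown because the article gives no share, and it is probably small: at an assumed 5%, the illustrative difference falls from 25.0 to 23.75 points. This is a minor improvement, worth making because it costs little and 99 of the 140 controls were still to be enrolled. It does not invalidate the comparison.

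**What to change.** - In 2.2.1, require that healthy subjects have no lifetime history of AMI, Takotsubo syndrome or breast cancer. Keep the ten-year limit for other major diseases.
- State in the same sentence whether the chronic-therapy clause means therapy at enrollment or therapy ever required.
- Review the clinical histories of the 41 healthy subjects already enrolled. Section 3.2.1 has these collected at the first meeting, so no new data are needed.
- Leave any former case found out of the patient-versus-healthy comparisons, and report how many there were.

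The cost is a line or two of eligibility text, a check of existing records and a slightly smaller pool of older controls.

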#### 2.2.2. Exclusion Criteria

Patients with a disability, cognitive impairment, life-threatening conditions, or enrollment in another clinical study will be excluded.

##### Sample Sizing

The size of the AMI group has been based on evaluation of the outcome data at one year from the results of the STEP-IN-AMI trial: a 43% incidence of the primary composite endpoint is expected in the psychotherapy group and 78% in the control group; therefore, 55 pts will be enrolled to achieve statistical power at the 95% confidence level with 80% power. Given the exploratory nature of the study in the other groups, which renders impossible any hypothesis on the effects of psychotherapy, statistical sample sizing has not been performed in these groups. To match the AMI group, 55 women with BC will also be enrolled. However, only 30 patients with TTS will be enrolled for feasibility reasons, due to the lower percentage of patients admitted to the hospital as compared to the other study groups which could unreasonably slow the enrollment phase. Consequently, it will be necessary to enroll 140 HS in the control group.

### 2.3. Therapies

Drug therapy in both the acute and chronic phase of the illness is left to the treating physician’s discretion and recorded in the case report. Psychopharmacological treatment is not part of this protocol but is recorded in the case report form.

Ontopsychological psychotherapy is a humanistic-existential treatment associated with psychodynamic analysis [29]. It is an original and complex synthesis derived from Freudian psychoanalysis, Jungian analytical psychology, and humanistic-existential psychology, as described by Abraham Maslow [40]. Ontopsychological theory considers the human being as a complex system whereby anything that happens in the body may influence the psyche and vice versa. The bidirectional connections between psyche and body may be considered scientifically based on several studies in the field of psycho-neuro-endocrine-immunology [41,42,43]. In this view, a psychotherapeutic intervention must improve global health to be considered efficacious. This approach includes a thorough analysis of unconscious dynamics, mainly represented by body emotions and dream material [29]. Ontopsychology introduces a new vision of the unconscious dimension, that is sustained by a positive nucleus, which has been called *“In-Self”* (In Sé). It characterizes our specific identity, acting through the vital drive that guides human life, and may be considered the criterion of nature, our specific identity which sustains us throughout life. Other fundamental and distinctive concepts of ontopsychology include: a different and more complex characterization of the *SuperEgo* than in psychoanalysis and a great importance given to the communication process, in particular non-verbal communication, represented both by Physiognomy-Kinesics-Proxemics, and the *semantic field* [44]. The semantic field is a concept developed by pioneers of the ontopsychological school. It is a specific aspect of unconscious communication, a complex interplay of psychic and biological data that emanate unconsciously from every person during all interpersonal interactions.

On the basis of its peculiar topographic and dynamic conception of the unconscious, the meaning of symbolic dream images has also been re-codified according to the theory of interpretation [45], with substantial differences compared to Freudian and Jungian psychoanalytic interpretation.

In particular, the unconscious dimension, sustained by the positive nucleus, In Sé, continuously communicates with the Ego of the person through some specific channels, represented by bodily sensations and emotions, and dreams. The In-Self may be considered a life-long psychic project, whose aim is represented by the optimal psycho-physical evolution of the subject, starting from the biological aspect that is the subject’s health, and extended to all of the personal and social aspects of life.

All patients will undergo counseling for cardiac risk factor modification and a healthy lifestyle. AMI patients will be referred to a CR program.

